## Abstract

**Background:**

Most adult intensive care units (ICUs) worldwide adopt restrictive family visitation models (RFVMs). However, evidence, mostly from non-randomized studies, suggests that flexible adult ICU visiting hours are safe policies that can result in benefits such as prevention of delirium and increase in satisfaction with care. Accordingly, the ICU Visits Study was designed to compare the effectiveness and safety of a flexible family visitation model (FFVM) vs. an RFVM on delirium prevention among ICU patients, and also to analyze its potential effects on family members and ICU professionals.

**Methods/design:**

The ICU Visits Study is a cluster-randomized crossover trial which compares an FFVM (12 consecutive ICU visiting hours per day) with an RFVM (< 4.5 ICU visiting hours per day) in 40 Brazilian adult ICUs. Participant ICUs are randomly assigned to either an FFVM or RFVM in a 1:1 ratio. After enrollment and follow-up of 25 patients, each ICU is crossed over to the other visitation model, until 25 more patients per site are enrolled and followed. The primary outcome is the cumulative incidence of delirium measured by the Confusion Assessment Method for the ICU. Secondary and tertiary outcomes include relevant measures of effectiveness and safety of ICU visiting policies among patients, family members, and ICU professionals. Herein, we describe all primary statistical procedures that will be used to evaluate the results and perform exploratory and sensitivity analyses of this study. This pre-specified statistical analysis plan was written and submitted without knowledge of the study data.

**Discussion:**

This a priori statistical analysis plan aims to enhance the transparency of our study, facilitating unbiased analyses of ICU visit study data, and provide guidance for statistical analysis for groups conducting studies in the same field.

**Trial registration:**

ClinicalTrials.gov, NCT02932358. Registered on 11 October 2016.

## Background

The recognition of the important role of family members in the intensive care unit (ICU) is the cornerstone of patient-centered care [1]. Beyond the justification of humanization, this strategy is proposed as a means to improve patient and family member outcomes [2]. In this context, small studies with a predominant before and after design have shown an association between flexible ICU visiting hours and reduced incidence of delirium in patients and increased satisfaction with care in family members [3–5]. Despite the growing recognition of the importance of family presence in the ICU, most ICUs around the world still adopt restricted visiting hours motivated by the ICU professionals’ perceptions of increased risk of disorganization of care, infection transmission, and burnout [6–9]. Unfortunately, few randomized studies have focused on the evaluation of the impact of different ICU visiting models on patients, family members, and ICU professionals, and this lack of evidence may constitute a barrier to the implementation of patient-centered care interventions in the ICU. The ICU Visits Study aims to investigate the effectiveness and safety of a flexible family visitation model (FFVM) vs. a restrictive family visitation model (RFVM) on delirium prevention among ICU patients, and to evaluate its potential benefits and hazards for family members and ICU professionals.

The present statistical analysis plan (SAP) aims to describe the trial’s analytical objectives and procedures before the end of the study recruitment and locking of the trial database to start analyses to comply with good clinical practice and avoid outcome reporting bias. This SAP was drafted without knowledge of any of the results of the investigators.

## Trial overview

The ICU Visits Study is a cluster-randomized, crossover trial comparing an FFVM (12 consecutive ICU visiting hours per day) with an RFVM (< 4.5 ICU visiting hours per day) in Brazilian adult ICUs. The study background, design, rationale, eligibility criteria, and sample size have been previously published [10]. In brief, mixed adult ICUs of public and private philanthropic hospitals with a restrictive policy of ICU visiting hours (< 4.5 h/day) are randomly assigned to either an FFVM or RFVM in a 1:1 ratio until the recruitment and follow-up of 25 patients (phase 1) (Fig. 1). After a 30-day washout period without subject recruitment, each ICU is switched over to the other visitation model (phase 2) until 25 more patients per site are enrolled and followed. The randomization is stratified by the number of ICU beds (1 to 10 or > 10 ICU beds) and performed using random block sizes of 2, 4, and 6. Consecutive patients aged ≥18 years admitted to the ICU, their closest family members, and bedside ICU professionals in each cluster are considered eligible for the present trial. A complete description of the inclusion and exclusion criteria is shown in Table 1.

**Fig. 1 Fig1:**
[figure not shown]
Study design. *FFVM* flexible family visitation model, *ICU* intensive care unit, *RFVM* restrictive family visitation model. All ICUs will have a learning period within the first 15 days of phases 1 and 2. During this period, ICUs will receive the intervention (FFVM or RFVM) but will not recruit subjects. Local investigators will use this period to adapt the ICU staff to the organizational aspects of study interventions

**Table 1 Tab1:** Eligibility criteria

	Inclusion criteria	Exclusion criteria
Cluster	Adult medical-surgical ICUs of public and philanthropic hospitals with at least six beds; restrictive policy of ICU visiting hours (< 4.5 h/day)	Structural or organizational impediments to flexible family visitation, according to the Brazilian resolution of minimal operational requirements for ICUs^a^
Patients	ICU patients aged ≥18 years	Coma (RASS − 4 or − 5) lasting > 96 h from the moment of first evaluation for recruitment; delirium at baseline (positive CAM-ICU); cerebral death; aphasia; severe hearing deficit; predicted ICU length of stay < 48 h; exclusive palliative treatment at ICU admission; unavailability of a family member to participate in the flexible family visits; unlikelihood to survive > 24 h; prisoner status; readmission to the ICU after enrollment in the study
Family members	Closest family member of a patient enrolled in the study	Family members who do not speak Portuguese or have serious difficulty in answering the self-applied questionnaires (e.g., due to illiteracy or severe visual or hearing limitations); having another family member already enrolled in the study
ICU professionals	Bedside ICU professionals (physicians, nurses, nursing technicians, and physiotherapists) who assist patients during daytime for at least 20 h/week at the enrolled ICU	ICU professionals who have a planned leave of absence of > 15 days during phase 1 of the study

*CAM-ICU* Confusion Assessment Method for the Intensive Care Unit, *ICU* intensive care unit, *RASS* Richmond Agitation-Sedation Scale

^a^Available from: http://bvsms.saude.gov.br/bvs/saudelegis/anvisa/2010/res0007_24_02_2010.html. Accessed 26 Aug 2017

In the FFVM, patients are allowed to receive visits from one or two close family members for up to 12 consecutive hours each day. Family members who agree to join the family visits have to attend a structured meeting at the ICU in which they receive guidance about the ICU environment, common ICU treatments, rehabilitation and basic infection control practices, multidisciplinary work at the ICU, and information on palliative care and delirium prevention. Additionally, family members receive an information brochure and are encouraged to access a website, both of which are designed to explain what happens during and after an ICU stay to legitimize emotions and improve cooperation with relatives without increasing the ICU staff workload. In addition to family visitation, patients in the FFVM are allowed to receive social visits at specific time intervals (according to the local ICU policies) from friends or other family members who did not qualify for flexible family visitation. In the RFVM, patients are allowed visitors according to routine ICU practices, but limited to the maximum of 4.5 h of visitation per day. Visitors are not required to attend the structured meeting in the RFVM.

The study primary outcome is the cumulative incidence of delirium during the ICU stay measured by trained researchers using the Confusion Assessment Method for the ICU (CAM-ICU) [11]. Secondary outcomes include daily hazard of delirium, ventilator-free days at day 7, any ICU-acquired infections according to the Centers for Disease Control and Prevention (CDC) criteria [12–14], ICU length of stay, and hospital mortality among the patients; symptoms of anxiety and depression measured by the Hospital Anxiety and Depression Scale (HADS) [15] and satisfaction measured by the Critical Care Family Needs Inventory (CCFNI) [16] among the family members; and prevalence of burnout syndrome evaluated by the Maslach Burnout Inventory (MBI) [17] among the ICU professionals. Tertiary outcomes include need for antipsychotic agents, need for mechanical restraints, unplanned loss of invasive devices (venous catheter, enteral tube, or urinary catheter), coma-free days at day 7, and ICU-acquired pneumonia, urinary tract infection, or bloodstream infection among the patients; self-perception of involvement in patient care among the family members; and satisfaction among the ICU professionals.

## Statistical analysis plan

### Overall principles

The main analysis for each outcome will be performed at the subject level using the intention-to-treat (ITT) principle, meaning that all participants with a recorded outcome will be included in the analysis and will be analyzed according to the treatment group to which they were randomized (FFVM or RFVM), independent of actual visiting hours. Moreover, all analyses will account for the cluster-randomized crossover design to ensure correct type I error rates and confidence intervals (CIs). A significance level of 0.05, adjusted for multiple comparisons when appropriate, will be used for all statistical comparisons. Analysis will start once all data to discharge for the last included patient have been obtained, the database has been cleaned and locked, and the SAP has been submitted for publication. The R Development Core Team software will be used for analysis [18].

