### Definition of analysis sets

At the cluster level, the ITT population includes all randomized ICUs that recruited subjects, regardless of the degree of adherence to the study interventions or achievement of the patient recruitment goal (50 patients per ICU). At the subject level, the ITT population includes all participants, regardless of protocol deviations. This includes patients who did not receive any ICU visits and family members who did not visit patients during the ICU stay, as well as patients who received visits longer than the maximum limit of visiting hours in both study periods (FFVM and RFVM).

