#### Primary outcome

All the pre-specified study outcomes are described in Table 3. The primary outcome is the cumulative incidence of delirium during ICU stay determined by the CAM-ICU, which was validated for the Brazilian population of critical care patients [21]. The cumulative incidence of delirium is defined as the presence of delirium (at least one positive CAM-ICU score) during the ICU stay. The differences in the incidences of delirium between the FFVM and the RFVM groups will be compared using generalized estimating equations with adjustment for the cluster effect, period effect, and interaction between intervention and period and presented as risk ratio (RR) and 95% CI.

**Table 3 Tab3:** Study outcomes

Outcomes	FFVM	RFVM	Type of effect estimate	Effect estimate (CI)	*p* value^a^
Primary					
Cumulative incidence of delirium:^b^ *n*/total *n* (%)	x/x (xx.x)	x/x (xx.x)	RR	x.xx (x.xx-x.xx)*	x.xx
Secondary					
Patients					
Daily hazard of delirium:^b^ mean (SD)	xx.x (xx.x)	xx.x (xx.x)	HR	x.xx (x.xx-x.xx)**	x.xx
Any ICU-acquired infection:^c^ *n*/total *n* (%)	x/x (xx.x)	x/x (xx.x)	RR	x.xx (x.xx-x.xx)*	x.xx
Proportion of ventilator free-days: mean (SD)	xx.x (xx.x)	xx.x (xx.x)	MD	x.xx (x.xx-x.xx)**	x.xx
ICU length of stay: mean (SD)	xx.x (xx.x)	xx.x (xx.x)	MD	x.xx (x.xx-x.xx)**	x.xx
Hospital mortality: *n*/total *n* (%)	x/x (xx.x)	x/x (xx.x)	RR	x.xx (x.xx-x.xx)**	x.xx
Family members					
HADS anxiety score: mean (SD)	xx.x (xx.x)	xx.x (xx.x)	MD	x.xx (x.xx-x.xx)***	x.xx
HADS depression score: mean (SD)	xx.x (xx.x)	xx.x (xx.x)	MD	x.xx (x.xx-x.xx)***	x.xx
CCFNI satisfaction score: mean (SD)	xx.x (xx.x)	xx.x (xx.x)	MD	x.xx (x.xx-x.xx)***	x.xx
ICU professionals					
Burnout syndrome:^d^ *n*/total *n* (%)	x/x (xx.x)	x/x (xx.x)	PR	x.xx (x.xx-x.xx)*	x.xx
Tertiary					
Patients					
Need for antipsychotic agents: *n*/total *n* (%)	x/x (xx.x)	x/x (xx.x)	RR	x.xx (x.xx-x.xx)*	x.xx
Need for mechanical restraints: *n*/total *n* (%)	x/x (xx.x)	x/x (xx.x)	RR	x.xx (x.xx-x.xx)*	x.xx
Unplanned loss of invasive devices: *n*/total *n* (%)	x/x (xx.x)	x/x (xx.x)	RR	x.xx (x.xx-x.xx)*	x.xx
Proportion of coma-free days: mean (SD)	xx.x (xx.x)	xx. (xx.x)	MD	x.xx (x.xx-x.xx)*	x.xx
ICU-acquired pneumonia:^c^ *n*/total *n* (%)	x/x (xx.x)	x/x (xx.x)	RR	x.xx (x.xx-x.xx)*	x.xx
ICU-acquired UTI:^c^ *n*/total *n* (%)	x/x (xx.x)	x/x (xx.x)	RR	x.xx (x.xx-x.xx)*	x.xx
ICU-acquired BSI:^c^ *n*/total *n* (%)	x/x (xx.x)	x/x (xx.x)	RR	x.xx (x.xx-x.xx)*	x.xx
Family members					

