## Discussion and trial status

In this SAP, we present the statistical procedures that will allow the comparison of effectiveness and safety outcomes between the FFVM and RFVM in the ICU Visits Study. The present publication aims to avoid risks of outcome reporting bias and data-driven results and provide guidance for statistical analysis for future studies in this field. As of March 2018, 40 ICUs were randomized. Currently, 1591 patients, 1192 family members, and 829 ICU professionals were included in the study. We expect that the recruitment of subjects will be completed in June 2018.

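### Correct type I error is promised for GEE analyses on at most 40 ICUs, but no small-sample variance correction or t reference is specified to secure it

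*SAP article*

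**What the plan says.** Overall principles makes a commitment on error control: "all analyses will account for the cluster-randomized crossover design to ensure correct type I error rates and confidence intervals (CIs". It sets the level as follows: "A significance level of 0.05, adjusted for multiple comparisons when appropriate, will be used for all statistical comparisons".

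The method meant to deliver this is GEE. For the primary outcome, the two groups "will be compared using generalized estimating equations with adjustment for the cluster effect", with further terms for period and for intervention by period. Secondary outcomes and Tertiary outcomes name GEE for everything except the daily hazard of delirium, which uses a joint survival model.

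The independent units are ICUs. The abstract (Methods/design) places the trial "in 40 Brazilian adult ICUs", and Discussion and trial status reports: "As of March 2018, 40 ICUs were randomized". Under Definition of analysis sets, "the ITT population includes all randomized ICUs that recruited subjects", so 40 is a ceiling.

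The document does not name the variance estimator, working correlation, small-sample correction or reference distribution. It names R as the software, without a package or option.

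**The concern.** GEE inference with a robust (sandwich) variance is valid as the number of independent clusters grows large. With 40 or fewer clusters, two approximations err in the same direction. The uncorrected sandwich variance is too small on average, and a normal reference has lighter tails than the statistic. Naming GEE and adjusting for cluster therefore does not by itself give correct error rates.

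The relative error grows in the tails. Table 3 sets 99% intervals for several patient secondary outcomes and 98.3% intervals for the family outcomes, so the multiplicity adjustment works where the approximation is weakest. A primary result near 0.05 could also fall on either side of the threshold depending on a choice that the plan leaves open.

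**Working it through.** **Inputs from the SAP.** Number of ICUs K = 40 at most. Allocation: "Participant ICUs are randomly assigned to either an FFVM or RFVM in a 1:1 ratio", so about 20 ICUs per sequence. Patients: "After enrollment and follow-up of 25 patients, each ICU is crossed over to the other visitation model", so 25 per ICU per phase. Alpha is 0.05, taken as two-sided because the plan reports 95% intervals.

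**The plan's own levels (Table 3).** 1 − 0.05/3 = 98.33% and 1 − 0.05/5 = 99.0%. Both reproduce the stated 98.3% and 99%. (The text of Secondary outcomes says 95% for the same outcomes. That is a separate matter, so all three levels are shown.)

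**Closed form.** This applies to the within-ICU treatment contrast in a two-sequence, two-period design. With K/2 ICUs per sequence, the uncorrected sandwich variance is (K/2 − 1)/(K/2) of the unbiased one, and the correctly scaled statistic follows t with K − 2 df. The actual error with a z reference is therefore

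2 × P(t(K−2) > z(1−α/2) × √[(K/2 − 1)/(K/2)]).

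At K = 40 the SE ratio is √(19/20) = 0.975. No event rate or ICC is needed.

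| Nominal | z | z × 0.975 | Actual, uncorrected SE + z | Actual, unbiased SE + z | t(38) critical value | CI widening needed |
|---|---|---|---|---|---|---|
| 5% | 1.960 | 1.910 | 6.4% | 5.7% | 2.024 | 2.024/1.910 = 1.06 |
| 1.67% | 2.394 | 2.333 | 2.5% | 2.2% | 2.505 | 2.505/2.333 = 1.07 |
| 1% | 2.576 | 2.511 | 1.6% | 1.4% | 2.712 | 2.712/2.511 = 1.08 |

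**Split of the excess at 5%.** Unrounded, the two error rates are 6.37% and 5.74%. Of the total excess of 1.37 points, 0.74 remains with an unbiased SE and z. Slightly more than half is thus due to z and the rest to the small SE.

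**Fewer ICUs.** At K = 30 the same formula gives 6.9%, 2.8% and 1.9%.

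**Simulation under the null.** There were 6,000 trials per setting, using log-link GEE with independence working correlation, ICU as cluster, and the planned terms for treatment, period and their interaction. The treatment effect was taken as the average over the two periods. Assumptions not in the SAP: event rate 10% or 20%; SD 0.5 between ICUs and 0.25 between periods within an ICU, on the logit scale; equal or unequal phase sizes. Monte Carlo SE is √(0.05 × 0.95/6000) = 0.28 points at 5% and √(0.01 × 0.99/6000) = 0.13 points at 1%.

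| K = 40 | Uncorrected SE + z | Mancl-DeRouen + t(38) |
|---|---|---|
| 5% | 6.5-6.8% | 4.3-5.0% |
| 1.67% | 2.2-3.1% | 1.3-1.7% |
| 1% | 1.5-2.1% | 0.7-1.1% |

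A further set of runs gave 5.8-7.0%, 2.1-3.1% and 1.3-2.2% for the uncorrected SE with z. In those runs Kauermann-Carroll with t(38) gave 4.3-5.5% at nominal 5%.

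**The case against.** The strongest reply is that the plan is silent here, and silence is not a choice of the wrong method. This is a journal article, and a variance option or df rule could sit in a fuller plan or in the analysis code. The sentence in Overall principles can also be read as simply ruling out analyses that ignore clustering.

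Much of this stands. A reader might infer that the trial's p-values and intervals are anti-conservative. The document does not support that, because nothing in it says that the uncorrected sandwich or a normal reference will be used. What remains is narrower. The plan states a guarantee, the named method alone does not deliver it at 40 clusters, and the abstract says that all primary statistical procedures are described here.

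Three further limits stand:

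- The inflation is small in absolute terms, and a too-small SE explains only about half of it.
- Mancl-DeRouen with t tends to fall slightly below nominal, so a correction can overshoot.
- Two extensions are tempting but not shown. Unequal ICU sizes from under-recruitment had no consistent effect: at K = 40 the error went from 6.5% to 6.8% at a 20% event rate and stayed at 6.5% at 10%. The Bonferroni-adjusted subgroup interaction tests were not simulated.

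**Conclusion.** The point holds as a gap between a stated guarantee and what the plan fixes. It is not an error already built into the results. If the uncorrected sandwich SE were used with z at 40 ICUs, type I error would be about 6-7% at nominal 5%, 2-3% at 1.67% and 1.3-2.2% at 1%. The relative excess is about 1.3-1.4 times at 5% and mostly 1.5-2 times at 1%.

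The closed-form values assume equal ICU weights and 20 ICUs per sequence. The simulated ranges also depend on the assumed event rates and variance components. The sizes apply to outcomes compared within ICUs across the two phases. They were not worked out for the two outcomes in ICU professionals, whose models have no period term. The joint model for the daily hazard of delirium is outside the point. The matter is worth correcting because the remedy is cheap and removes an analyst's choice that could decide a borderline result.

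**What to change.** Before database lock, add to Overall principles that every GEE analysis (a) treats the ICU, not the ICU-period, as the cluster, (b) uses a bias-corrected sandwich variance, preferably Kauermann-Carroll because Mancl-DeRouen is slightly conservative, and (c) takes p-values and intervals from a t distribution with about (number of contributing ICUs − 2) df, which is 38 if all 40 contribute.

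The cost is a sentence or two in the SAP and a change to the variance and reference settings in the analysis code. At 40 ICUs, intervals are about 6% (95%), 7% (98.3%) and 8% (99%) wider than with the uncorrected SE and z, with a corresponding small loss of power. Recruitment was still open when the article was written, so the choice could be fixed without knowledge of results.

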### Handling of missing data

We anticipate minimal missing values, given that the study variables will be determined during hospital stay by trained researchers. Nevertheless, the coordinator center will contact site investigators to retrieve any missing data values.

ICUs with incomplete subject recruitment (e.g., less than 50 patients) will be included in the primary analysis for the study outcomes considering all subjects available in the cluster. To assess the risk of bias related to ICUs that did not achieve the patient recruitment goal, multiple imputation techniques will be performed for the primary outcome and presented as sensitivity analyses. The missing values for the variables that compose the HADS, CCFNI, and MBI will be imputed, replacing the missing items with the mean of the answered items in the same subscale, if at least half of that subscale has been answered. The missing values for the variables that compose the PREdiction of DELIRium in ICU patients (PRE-DELIRIC) score will be imputed in a similar way as in the original study [19]. We will assume that if a variable is not determined, most likely the missing variable has a normal or negative value (e.g., no infection, no metabolic acidosis) or a mean value (e.g., Acute Physiology and Chronic Health Evaluation-II [APACHE-II] score) of the study population. We will not perform any imputation for the length of ICU visits per patient per day.

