#### Sensitivity analyses for the primary outcome

We aim to conduct the following sensitivity analyses for the primary outcome to assess consistency and the risk of bias:Evaluation of study intervention effects adjusted by the baseline risk of delirium according to the PRE-DELIRIC score.Evaluation of study intervention effects considering the cluster adherence to FFVM implementation. In this analysis, the study intervention effects will be adjusted by the total fidelity of FFVM implementation score.Evaluation of study intervention effects considering the potential confounding effect of sedation on the delirium diagnosis. In this analysis, the study intervention effects will be evaluated, considering patients with positive CAM-ICU during ICU stay in the context of Richmond Agitation-Sedation Scale (RASS) score – 2 or − 3 as non-delirious subjects.Evaluation of effects of study interventions, considering a best plausible scenario/worst plausible scenario imputation of outcomes among ICUs that did not complete the patient recruitment as follows:*Best plausible scenario*: Imputation of the lowest study cluster/phase incidence of delirium for missing FFVM patients and the highest study cluster/phase incidence of delirium for missing RFVM patients*Worst plausible scenario*: Imputation of the lowest study cluster/phase incidence of delirium for missing RFVM patients and the highest study cluster/phase incidence of delirium for missing FFVM patients.

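### The missing-outcome sensitivity analyses target patients who were never recruited; enrolled patients without a CAM-ICU outcome are not covered

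*SAP article*

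**What the plan says.** Four places in the SAP article bear on this.

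- **Handling of missing data.** ICUs that enrol fewer than 50 patients "will be included in the primary analysis for the study outcomes considering all subjects available in the cluster". To examine possible bias from "ICUs that did not achieve the patient recruitment goal, multiple imputation techniques will be performed for the primary outcome", as sensitivity analyses. For missing values in general, sites are queried. Imputation rules are given for HADS, CCFNI and MBI items and for PRE-DELIRIC components. None is given for a missing CAM-ICU outcome in an enrolled patient.
- **Sensitivity analyses for the primary outcome.** The best scenario for ICUs that did not complete recruitment is "Imputation of the lowest study cluster/phase incidence of delirium for missing FFVM patients", with the highest cluster/phase incidence used for the RFVM shortfall. The worst scenario swaps the two. No minimum size is set for the cluster-phase that supplies the extreme value.
- **Overall principles.** ITT is explained as "meaning that all participants with a recorded outcome will be included in the analysis", by randomized group.
- **Definition of analysis sets.** "At the subject level, the ITT population includes all participants, regardless of protocol deviations".

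**The concern.** Both imputation analyses are triggered by missing the recruitment goal, not by a missing outcome. The people being imputed have no baseline data and no follow-up; all that is known is the ICU, phase and arm they would have belonged to. An analysis of that kind cannot show whether under-recruitment biased the comparison, which is the purpose the plan gives for it.

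The missing outcomes that can bias a comparison of enrolled patients are those of people who entered the trial and have no usable CAM-ICU result. They drop out of the main analysis under one description of ITT and belong to the population under the other, and no planned sensitivity analysis deals with them. Readers of the final report could then take the best/worst range as a statement about missing outcomes when it mostly describes how many patients were not recruited.

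**Working it through.** **Step 1: the plan's own figures.** The goal is 25 patients in each of two phases: 25 + 25 = 50 per ICU, as stated. With 40 ICUs, full recruitment is 40 × 50 = 2000 patients in 40 × 2 = 80 cluster-phases. The article reports 1591 patients included at the time of writing, 2000 − 1591 = 409 short (20.45%). Recruitment was still open, so this is not the final shortfall.

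The article gives no incidence, ICC, final shortfall or missing-outcome rate. All such values below are assumptions.

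**Step 2: multiple imputation of unrecruited patients.** Assume 20% delirium in both arms, 800 of 1000 planned patients recruited per arm, no covariates, and no clustering. The variance of log RR is the sum over arms of 1/x − 1/n, where x is the number of events.

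- Recruited only: x = 160, n = 800. SE = √[2 × (1/160 − 1/800)] = √0.0100 = 0.100 (simulated mean 0.1002).
- After multiple imputation with Rubin's rules: simulated mean SE 0.1003; mean absolute change in log RR about 0.002.
- If filled-in records were counted as observed: x = 200, n = 1000. SE = √[2 × (1/200 − 1/1000)] = √0.0080 = 0.089 (simulated mean 0.090).

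Properly combined, the imputation adds nothing to the available-case result. This illustration has no ICU terms. A model with ICU terms could reweight ICUs towards equal size, which was not computed, but it would still use no information beyond the recruited patients.

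**Step 3: best/worst scenario with a true RR of 1.** Let p be the incidence, s the shortfall (equal in both arms), and lo and hi the lowest and highest cluster-phase incidences. Then

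best RR = [(1 − s)p + s·lo] / [(1 − s)p + s·hi], and worst RR = 1 / best RR.

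The values of lo and hi are mean extremes of 80 simulated beta-binomial cluster-phases of 25 patients. For p = 0.20 and ICC 0.05 they are 0.003 and 0.541. At s = 0.05:

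(0.95 × 0.20 + 0.05 × 0.003) / (0.95 × 0.20 + 0.05 × 0.541) = 0.19015 / 0.21705 = 0.876; reciprocal 1.141.

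Across p = 0.10, 0.20, 0.30 and ICC = 0.01, 0.05:

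| Shortfall | Best RR | Worst RR |
|---|---|---|
| 2% | 0.93-0.97 | 1.03-1.08 |
| 5% | 0.83-0.92 | 1.08-1.21 |
| 10% | 0.70-0.85 | 1.17-1.44 |
| 20% | 0.50-0.73 | 1.38-1.99 |

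No enrolled patient has a missing outcome in any of these cases. The range widens only because s, lo and hi change.

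**Step 4: what is left uncovered.** Let m be the proportion of enrolled patients without an outcome, equal in both arms, with p = 0.20 among the rest. If all missing FFVM patients are negative and all missing RFVM patients positive, RR = (1 − m)p / [(1 − m)p + m]; the reverse gives the reciprocal.

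- m = 1%: 0.198 / 0.208 = 0.95; reciprocal 1.05.
- m = 3%: 0.194 / 0.224 = 0.87; reciprocal 1.15 (1.155 to three decimals).
- m = 5%: 0.190 / 0.240 = 0.79; reciprocal 1.26.

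These are extreme bounds, not expected bias. They show that even a small proportion is worth a planned check.

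**The case against.** The strongest reply is that in a crossover with a fixed quota per phase, a shortfall is not always just a smaller cluster. An ICU that stops before or during its second phase loses a planned cluster-period after randomization, and its reasons may relate to the visitation model. The worry about bias is therefore legitimate. That stands, but imputing patients on whom nothing was recorded does not measure this bias. Nor does restricting to ICUs that completed both phases, because it selects on the same post-randomization event.

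Other replies also hold in part:

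- The plan expects few missing values and will query sites. Table 1 excludes prolonged coma, predicted short stays and patients unlikely to survive 24 hours. The daily-hazard analysis models delirium jointly with death or ICU discharge. The flow diagram will show follow-up losses. It would therefore be too strong to say that the plan ignores enrolled patients who leave early. What is missing is a sensitivity analysis of the primary outcome for them.
- The two ITT descriptions can be read as naming the population in one place and who can be modelled in the other. This is a mild inconsistency, although the first is worded as a definition.
- A reader might infer that standard errors will be too small because the sample is inflated. Rubin's rules do not do this (0.1002 against 0.1003), and the article does not say that scenario fills will be counted as observed records.
- A reader might also call the extreme incidences mostly sampling noise. Chance alone does spread them: at 20% with no between-ICU variation they average about 3% and 41%. How much of the observed spread would be chance depends on an ICC that the article does not give.

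**Conclusion.** The point holds as one about the target of the sensitivity analyses. As planned, multiple imputation restates the available-case result. The best/worst scenario produces an RR range that follows the recruitment shortfall and the extreme cluster-phases: with no true effect, roughly 8-17% below 1 in the best case and 8-21% above 1 in the worst at a 5% shortfall. These sizes rest on the assumed incidence, ICC, equal shortfall by arm and cluster-phases of 25. Enrolled patients without a CAM-ICU outcome have no corresponding analysis; how many there will be is unknown.

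A reader might infer that the primary result itself could be overturned or propped up by imputed data. The article does not support that: the primary analysis uses available subjects, and both imputations are labelled as sensitivity analyses, so the primary estimate, interval and p value do not change. The correction is worth making, but it does not threaten the main analysis.

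**What to change.** 1. Remove multiple imputation and the best/worst fills for unrecruited patients.
2. Define the ITT population once, as all enrolled patients analysed by randomized group, and state that the main analysis uses those with a recorded outcome.
3. Apply multiple imputation only to enrolled patients without a CAM-ICU outcome, using PRE-DELIRIC, APACHE-II, ventilation, ICU stay, vital status, ICU and period. Add best/worst bounds by arm for the same patients.
4. For under-recruitment, keep the available-subject primary analysis. As a supplementary check only, repeat the same model in ICUs that completed both phases, noting that this selects on a post-randomization event and does not bound the bias.

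The cost is minor SAP wording and a change to the sensitivity code. No new data are needed.
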